##### Dose-Response exploration

The type of activity, its frequency, duration, and intensity (i.e., according to the Borg scale) will be considered to compute the dose of physical exercise. The weekly dose of physical exercise will be converted in kcal and in METs using the Compendium of Physical Activities (i.e., coding scheme classifying specific physical activities by their rate of energy expenditure) [68, 69]. The effect of physical exercise dose on cognitive and physical functions will be evaluated according to participants’ mean weekly dose during the 6 months of intervention. Based on the overall study sample distribution, participants will be classified into three groups: higher, medium, and lower doses of physical exercise (i.e., tercile split). How the dose of physical exercise affects the primary and the secondary outcomes will be addressed by a repeated measures ANCOVA model, adjusted for age, sex, and education, including the effects of the intervention (physical exercise alone or combined with cognitive training), time (pre at baseline, mid at 3 months, post-intervention at 6 months) and dose groups (lower, medium or higher doses). An exploration of the dose-response effect for cognitive training will also be performed within the combined physical exercise and cognitive training intervention group. The dose of cognitive training will be considered according to its mean weekly duration. How the dose of cognitive training affects the primary and the secondary outcomes will be addressed by a repeated measures ANCOVA model, adjusted for age, sex, education, and the dose of physical exercise, including the effects of time (pre at baseline, mid at 3 months, post-intervention at 6 months) and dose groups (lower or higher doses of cognitive training; median split).

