### Remote setting and procedures, online data management

There is no on-site visit planned in the course of the study. The research team has implemented online tools that allow performing all assessments, exercise monitoring, and cognitive training entirely remotely. The research project will be advertised to active members of physical exercise centers and to community-dwelling adults through online study announcements (e.g., videos, interviews, newsletters). Potential participants will be able to express their interest by leaving a voice mail or sending an email to an email address dedicated to the study. The name and contact information of potential participants will be compiled in a password-protected encrypted file located in a cloud folder with restricted access. The anonymization table is built at this stage, where each contact is associated with an anonymous study I.D. number. A two-stage screening process will be used to select participants (timepoint T-1; Table 1). Initial contact will be made over the phone by a member of the research team. During this pre-screening call, only potential participants with no major physical or medical limitations to exercise and with access to the Internet and necessary technology will be selected. They will then receive the information and consent form by email, and the preliminary call will be scheduled with a member of the research team. During the preliminary call, the information and consent form will be presented to the potential participants, and they will be given the opportunity to provide oral consent. They will then be required to send written consent by email. If oral consent is obtained, the cognitive (MMSE) and physical (PARQ+) screenings will then be performed with a research assistant and will later be reviewed by a neuropsychologist and a kinesiologist, respectively. Once the research team receives the written consent by email and ensures eligibility, the participant will be considered enrolled. A technology tutorial will then be scheduled to ensure that Internet access and tools are ready and sufficiently mastered by participants. Collection of measurements and training data all along the study will be managed by assessors and trainers using online case report forms specifically dedicated to each testing session. Participants will receive automatic standardized communications by email to transmit study information like appointment schedules, links to self-reported questionnaires, and training guidelines. A non-overwriting process will ensure data integrity: all form submissions will be recorded in a journal fashion. Moreover, all data entries will be traceable and associated with a timestamp along with the identity of the research team member who completed the data entry. To ensure the blinding of the study, data collection will be divided into two sections on the online platform: training and evaluations. Research team members will receive different access based on their roles. The above-described procedure is summarized in Fig. 1.

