### Data analysis

#### Sample size calculation

The Montreal Health Innovations Coordinating Center**’**s biostatistics team completed the sample size calculation. The calculation was based on values available in the literature for physical exercise training alone [67], on different plausible values for the combined physical and cognitive training (since there are no values in the literature for this group), and on clinically relevant effect sizes to detect the cognitive outcome. A sample size of 49 subjects in each group will have 80% power to detect a difference in means of **−** 0.186 (the difference between a physical training alone mean of 0.239 and a combined training mean of 0.425, for an effect size of 0.624), assuming that the common standard deviation is 0.298 using a two-group *t* test with a 0.050 two-sided significance level. Considering a 20% attrition rate observed in our previous exercise studies, 61 participants will be recruited per intervention arm to ensure the targeted 49 participants per group (61 * .80 = 49) for a total of 122 participants.

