## Study limitation and development perspectives

Despite its strengths mentioned above, the proposed design presents some limitations. Due to this exceptional pandemic context, some ethical considerations refrained the research team from implementing a control group. Nevertheless, to address this limitation, at least partially, all participants will be included in the final analyses, without exclusion based on participation, to document the dose-response relationship between physical exercise and outcome effects. Additionally, sex was not taken into account in recruitment and randomization processes, although sex differences have been reported on cognition [74], as well as in exercise-training effects on cognition in healthy older adults [75]. Consequently, sex will be considered as a covariate in all statistical analyses. Also, a recent study from Peterman et al. [76] highlights that longitudinal changes in nonexercise prediction equations of cardiorespiratory fitness were associated with changes in cardiorespiratory fitness as measured by standardized VO2_max_ protocols but present significant errors in their predictions. Therefore, the use of nonexercise prediction equations could lead to a significant error in the estimated change of participants' cardiorespiratory fitness.

Future studies using more direct physical fitness assessments and tracking devices for remote monitoring could help better inform on the effect of physical exercise training in seniors. Indeed, adding a direct measure of physical fitness could help inform on participants' physical condition when they engage themselves in the intervention, as well as their progression. Its combination with a measurement of frequency, duration, and intensity of physical exercise sessions provided by tracking devices such as smartwatches or smart garments may shed light on the relationship between exercise training characteristics and the changes in physical fitness over the course of the intervention. This kind of information may substantially improve remote monitoring, helping the training coaches provide resources and recommendations adapted to each participant according to their physical fitness and progression.

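### The exploratory dose-response models cut a self-chosen dose into groups, use a six-month average dose for the three-month score, and do not list prior physical activity as a covariate

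*Protocol article*

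**What the plan says.** The Dose-Response exploration section of the protocol article fixes these choices:

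- **Physical exercise.** Dose is the mean weekly dose over the six-month programme, expressed in kcal and in METs. On the overall sample distribution, "participants will be classified into three groups: higher, medium, and lower doses of physical exercise (i.e., tercile split". The repeated-measures ANCOVA has arm, time (baseline, 3 and 6 months) and dose group as effects, adjusted for age, sex and education.
- **Cognitive training.** Within the combined arm only, mean weekly duration enters as "dose groups (lower or higher doses of cognitive training; median split". The adjustment is the same plus physical dose. The averaging window is not named.

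Other sections matter here. Under Interventions, participants may set their own dose. Under Remote monitoring and counseling, coaches collect dose every week and adapt their advice to it. The study is "advertised to active members of physical exercise centers and to community-dwelling adults". Table 1 places the Physical Activity Scale for the Elderly at T0, and Other variables names prior activity as a possible moderator. The limitations section explains that there is no control group and says that, to address this at least partly, everyone will be analysed "to document the dose-response relationship between physical exercise and outcome effects".

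**The concern.** Three separate weaknesses meet in one analysis.

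1. **Information.** A quantity recorded weekly is reduced to three or two groups at cut-points that depend on the sample. Differences in dose within a group are then ignored.
2. **Timing.** A participant's group is set partly by exercise in months 4 to 6, yet it is used to explain the 3-month score. Exposure after an outcome cannot have caused it, and may even respond to how the participant was doing at month 3.
3. **Confounding.** Dose is chosen, not randomised. People who were already active may choose higher doses and may also change more, or less, over six months. Neither dose model lists prior activity as a covariate.

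At stake is whether a dose gradient, or its absence, can be read as an effect of dose. The limitations section gives the analysis some weight as partial compensation for the missing control group, and no section says that the association is observational.

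**Working it through.** **The plan's own figure.** No power is stated for the dose-response analysis. The only calculation is for the two-arm comparison: "A sample size of 49 subjects in each group will have 80% power", "for an effect size of 0.624", "assuming that the common standard deviation is 0.298", "with a 0.050 two-sided significance level". The effect size reproduces: 0.186/0.298 = 0.624. The sample size does not: the stated inputs need 41 per group (normal formula) or 42 (exact t), and 49 per group gives 86.4% power. That is a separate and conservative discrepancy with no bearing here. Only the completer counts are carried forward: 49 in the combined arm and 98 in all.

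**Information kept by grouping** (assumptions: normal dose, linear effect)

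- Terciles: cuts at z = ±0.4307. The mean of an outer third is 3φ(0.4307) = 1.091. Share of dose variance kept = (2/3) × 1.091² = 0.793.
- Median split: mean of a half is 2φ(0) = 0.798. Share kept = 0.798² = 2/π = 0.637.

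**Effect on power** (noncentral F for one change score, λ = N·r²/(1 − r²), four covariate degrees of freedom, alpha 0.05; the dose-outcome correlation ρ is assumed). For groups, r² is ρ² times the share kept.

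| Analysis | ρ | Continuous dose | Planned grouping |
|---|---|---|---|
| Physical, N = 98, 2-df tercile factor | 0.20 | 52% | 33% |
| | 0.275 | 80% | 59% |
| | 0.30 | 87% | 67% |
| | 0.40 | 99% | 92% |
| Cognitive, N = 49, median split | 0.30 | 58% | 39% |
| | 0.379 | 80% | 58% |
| | 0.40 | 85% | 64% |

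Part of the tercile loss is the second degree of freedom. At ρ = 0.275 a 1-df trend across terciles has 70% power. At ρ = 0.30 a 2-df quadratic in continuous dose has 79%, against 67% for the tercile factor.

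**Dependence on scale.** Suppose dose is log-normal with log SD 1. If the effect is linear in raw dose, terciles keep only 40%. If it is linear in log dose, terciles still keep 79% while a straight line in raw dose keeps 58%. With log SD 0.5 the corresponding figures are 67% for terciles (raw effect) and 88% for the raw line (log effect).

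**Timing.** Let c be the assumed correlation between the mean doses of the first and second three months. The 0-3-month dose correlates √((1 + c)/2) with the six-month mean: 0.87, 0.92 and 0.97 for c = 0.5, 0.7 and 0.9. By simulation, 30%, 23% and 13% of participants then fall in a different tercile from the one their 0-3-month dose would give.

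**Confounding with no true dose effect.** Let prior activity correlate a with dose and b with outcome change (assumed: a 0.3 to 0.7, b 0.1 to 0.3). The spurious gap between top and bottom terciles is 2 × 1.091 × a × b:

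- a = 0.3, b = 0.1: 0.07 SD of change, false-positive rate 5.5% (N = 98);
- a = 0.7, b = 0.3: 0.46 SD, false-positive rate 36%.

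A continuous dose without the covariate would show 6% and 56% in the same two settings, because it detects the confounded association more readily. The first and third changes therefore belong together.

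**The case against.** The strongest reply is that this is an exploration and is labelled so. Dose-response is not one of the two numbered aims in the Background, it is absent from the Hypotheses, and no efficacy criterion in Planned data analysis rests on the dose groups. A reader might infer that a main trial aim is compromised, and the documents do not support that. This part of the reply stands and limits the weight of the point.

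Four further readings go beyond the text:

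- **Prior activity is ignored altogether.** Other variables lists the scale as a possible moderator and ends by saying that these scales will serve as covariables, with motivation as the reason. The sentence follows the satisfaction questionnaire and most naturally refers to it, but could cover the whole list. What holds is that the dose models do not list prior activity and the two sections need reconciling.
- **Most participants come from exercise centres.** Recruitment also addresses community-dwelling adults, and no proportion is given.
- **The dose measure merely reflects body weight, because kcal does.** METs are planned beside kcal.
- **The authors claim to have replaced a control group.** They claim only partial compensation.

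Two technical replies also have force. Terciles are unaffected by a skewed dose scale and can show a plateau, so a straight line in raw dose may do worse than the plan. And the timing fault affects only the 3-month score: for the contrast from baseline to month 6, a six-month dose matches the outcome. Neither reply defends the tercile factor against a continuous dose on a suitable scale, or the use of later exposure at month 3.

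**Conclusion.** The point holds for an exploratory analysis. Under a normal dose and a linear effect, terciles keep about 79% and a median split about 64% of the information. An effect that a continuous term would find with 80% power then has 59% (physical, 98 completers) or 58% (cognitive, 49 completers). The gain is not guaranteed on every scale of dose. The 13% to 30% of participants placed in a different tercile, and the spurious gap of 0.07 to 0.46 SD, rest on assumed correlations and show plausible ranges only. The direction of any confounding is unknown. The structural facts need no assumption: dose is self-chosen, later exposure enters the classification for the 3-month score, and prior activity is not among the listed covariates of either dose model. The change is worth making, but the randomised comparison between arms does not depend on it.

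**What to change.** Before outcome data are analysed:

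1. Make a continuous dose the main dose-response analysis: a MET-based weekly dose on a suitable scale (log, or with a spline), and cognitive-training minutes per week likewise. Keep terciles and the median split as a descriptive display.
2. Relate the 0-3-month dose to the 3-month score and the 0-6-month dose to the 6-month score. State the averaging window for cognitive training too.
3. Add the T0 Physical Activity Scale for the Elderly as a covariate, and reconcile Other variables with Dose-Response exploration on which scales enter which model. Estimated fitness adds little, since the Matthews estimate is itself built largely from age, sex and self-reported activity.
4. If the T0 outcome score is used as a covariate, take baseline out of the response. It should not be both a covariate and a level of time.
5. State in Dose-Response exploration and in the limitations section that the association is observational and does not stand in for a control group.

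The cost is analysis wording, since every variable is already collected. The drawbacks are that a functional form must be chosen, and that confounding is reduced but not removed, because dose remains self-chosen, self-reported and influenced by weekly coaching.

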### Interventions

After being randomly (see the “Randomization and blinding” section) assigned to one of the 2 study arms, participants will receive a group-specific training guide. The training guide contains recommendations about the nature, intensity, and frequency of the training sessions. Participants will then attend an introductory session over the phone given by their training coach. Participants will be invited to follow the training guide while adjusting their dose as they see fit.

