#### Remote monitoring and counseling

Once a week, training coaches will call participants over the phone to (1) motivate them to stay engaged in their training and to (2) collect exercise and cognitive training data reported by participants in their follow-up agenda during the previous week. The training coach will also provide and update information about training resources available online, track adherence, and advise participants according to their training characteristics and study training guidelines. Information about physical exercise and cognitive training sessions collected during these calls will allow to track the weekly dose of exercise and cognitive training and to adapt the recommendations given to the participant accordingly.

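### The exploratory exercise-dose model adjusts for arm but not for individual cognitive-training dose, so its dose contrast is confounded if the two self-chosen doses correlate in the combined arm

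*Protocol article*

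**What the plan says.** The section Dose-Response exploration writes out two models with different covariate lists.

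- **Exercise-dose model.** Both arms are pooled and split into terciles of mean weekly exercise dose over the whole sample. The effect of exercise dose "will be addressed by a repeated measures ANCOVA model, adjusted for age, sex, and education, including the effects of the intervention", time and dose group. Individual cognitive-training dose does not appear.
- **Cognitive-dose model.** This analysis "will also be performed within the combined physical exercise and cognitive training intervention group". It is "adjusted for age, sex, education, and the dose of physical exercise, including the effects of time" and a median split of cognitive dose. Here the other dose is a covariate.

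The missing covariate is collected and defined. In the same section: "The dose of cognitive training will be considered according to its mean weekly duration". Under Remote monitoring and counseling, one weekly call gathers the information on both trainings, which "will allow to track the weekly dose of exercise and cognitive training". Under Interventions, the dose is left to the participant: "Participants will be invited to follow the training guide while adjusting their dose as they see fit".

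**The concern.** In the combined arm, the same coach call encourages and records both trainings, and participants set their own amounts. People who engage with one may well engage with the other. If cognitive gain rises with cognitive dose, high exercisers in that arm would then gain more for a reason other than exercise. An arm indicator cannot remove a gradient within an arm, and randomisation does not protect a contrast between self-selected dose groups.

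The plan recognises this overlap in one direction only. The stake is the reading of the exercise dose-response. The end of the Background gives it as something the study will explore, and the limitations section offers it as partial compensation for having no control group. The between-arm comparison is not at stake.

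**Working it through.** **Inputs from the article (Sample size calculation).** Means 0.239 (exercise alone) and 0.425 (combined), difference 0.186; SD 0.298; 49 per arm. The stated effect size reproduces: 0.186/0.298 = 0.624. The stated 80% power does not: 49 per group gives 86.4% with the two-sample t test. That is a separate matter with no bearing here. The article gives no figure for the dose models themselves.

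**Assumptions, not in the article.**
- True exercise-dose effect: zero.
- Benefit of cognitive training proportional to its dose.
- Coefficient of variation of cognitive dose (CV): 0.5 to 0.8.
- Correlation of the two doses in the combined arm (ρ): 0.3 to 0.7, with 0 and −0.3 also examined.
- Both doses normal; exercise dose distributed alike in the two arms.

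**Formula.** Write the 6-month gain as 0.239 + 0.186 × G × (1 + CV × C) + error. G is 1 in the combined arm and 0 otherwise; C is standardised cognitive dose.

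1. The means of the top and bottom thirds of a standard normal variable differ by 2 × 3 × φ(0.431) = 6 × 0.3636 = 2.18.
2. In the combined arm, C therefore differs between the outer exercise terciles by 2.18 × ρ.
3. The false contrast within that arm is 0.186 × CV × 2.18 × ρ = 0.406 × CV × ρ.
4. Pooled over two equal arms, with arm in the model, it is half of that: **0.203 × CV × ρ**.

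| ρ | CV 0.5 | CV 0.8 |
|---|---|---|
| −0.3 | −0.030 | −0.049 |
| 0 | 0 | 0 |
| 0.3 | 0.030 | 0.049 |
| 0.5 | 0.051 | 0.081 |
| 0.7 | 0.071 | 0.114 |

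From ρ = 0.3, CV 0.5 to ρ = 0.7, CV 0.8, the pooled bias is 16% (0.030/0.186) to 61% (0.114/0.186) of the assumed benefit.

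**Simulation of the planned structure (arm plus pooled terciles, 6-month gain).** At ρ = 0.5 and CV 0.5 the false contrast is 0.051 and the test rejects about 10% of the time at a nominal 5%. In a wider run over ρ 0.3 to 0.7 and CV 0.5 to 0.8, the bias is 0.029 to 0.096, a little below the formula at the upper end, and rejection is 6.2% to 23.3%. With exercise dose alike in the two arms, the arm coefficient stays at 0.184 to 0.188 throughout, so the average benefit is credited to arm.

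**After adding cognitive dose (ρ = 0.5, CV 0.5).** The false contrast falls to 0.002 or less and rejection to about 5%. The standard error of the contrast rises only from 0.075 to 0.078.

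**Coding.** If dose is entered as raw minutes, with zero in arm 1, the arm term becomes an extrapolation to no cognitive training within the combined arm. In this scenario its coefficient falls from 0.186 to about 0 and its standard error rises from 0.061 to 0.111. With dose centred within the combined arm, the coefficient stays at 0.186 with a standard error of 0.061.

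**If adherence itself affects the gain.** A common adherence factor worth 0.05 per SD, again at ρ = 0.5 and CV 0.5, gives a false contrast of about 0.13 as planned, about 0.063 after adding cognitive dose, and about 0.075 in arm 1 alone.

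**The case against.** A reader might infer that the benefit of cognitive training as a whole is credited to exercise dose. The article does not support that: intervention arm is a factor in the same model and absorbs the average benefit. Only the part that varies with cognitive dose and also tracks exercise dose can leak.

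A reader might also infer that the plan will yield a spurious synergy finding. The leak does sit in the combined arm only, but the section names no dose-by-arm test, so this is a caution for interpretation and not a defect of a stated test. If the three listed factors were crossed, arm 1 would give a gradient free of cognitive dose, while the combined arm's would stay confounded.

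Other points on that side:

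- **The asymmetry has a partial rationale.** In the pooled model, arm stands in for cognitive training, which arm 1 does not receive. The cognitive-dose model is fitted in one arm, where no arm term is possible. This explains the difference but leaves the within-arm gradient untouched.
- **Size and sign are unknown.** The article gives no correlation. Cognitive sessions must precede exercise or follow it by at least 3 hours, so the two could compete for time. Exercise dose is in kcal and METs, cognitive dose in duration, which may weaken the link. At ρ = 0.3 and CV 0.5, rejection is only 6.2%. All of this stands.
- **Self-selection is the larger limitation.** This stands too, as the adherence scenario shows. Under Other variables, satisfaction scales are to serve as covariables for motivation, but they do not measure cognitive dose and are not in the list for this model.
- **The analysis is exploratory.** The numbered aims, the hypotheses and the two efficacy criteria do not use it. This limits the severity.

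**Conclusion.** The point holds in a limited form and is minor. As written, the exercise-dose contrast is open to confounding by cognitive-training dose in the combined arm, a confounder that the trial records and that the companion model treats in the reverse direction. Under the assumptions stated, the bias is roughly +0.03 to +0.11 for correlations of 0.3 to 0.7, about −0.03 at −0.3 (CV 0.5), and nil at zero correlation. It would also vanish if gain did not depend on cognitive dose.

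It would be wrong to conclude that adjustment, or restriction to arm 1, makes the exercise-dose estimate unbiased. Each removes confounding by cognitive dose only. Dose is self-chosen, so the dose-response remains observational.

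**What to change.** In the exercise-dose model, add mean weekly cognitive-training duration, centred at the combined-arm mean for participants in that arm and set to zero in arm 1, together with its interaction with time. Report the exercise-dose estimate from arm 1 alone as a sensitivity analysis. State in the plan that these steps deal with cognitive dose only, that confounding by general adherence or motivation remains, and that the dose-response is read as observational.

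No new data are needed. The dose contrast becomes slightly less precise (standard error 0.075 to 0.078 at ρ = 0.5 and CV 0.5), and more so if the doses are strongly correlated. The arm 1-only estimate is much less precise: with about 49/3 people per tercile its standard error is 0.298 × √(2/(49/3)) = 0.104, against 0.298 × √(2/(98/3)) = 0.074 for the pooled sample by the same formula. It serves as a check and not as a replacement.
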